**Methods:**

This project uses a blocked randomized cohort design with an active comparison control (ACC) condition. We will recruit and include approximately 276 teachers from 46 schools randomly assigned to BASIS-T or ACC conditions. Aim 1 will evaluate the main effects of BASIS-T on proximal implementation mechanisms (attitudes, subjective norms, self-efficacy, intentions to implement, and maintenance self-efficacy), implementation outcomes (adoption, reach, fidelity, and sustainment), and child outcomes (SEB, attendance, discipline, achievement). Aim 2 will examine how, for whom, under what conditions, and how efficiently BASIS-T works, specifically by testing whether the effects of BASIS-T on child outcomes are (a) mediated via its putative mechanisms of behavior change, (b) moderated by teacher factors or school contextual factors, and (c) cost-effective.

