Aim 2 will evaluate the effects of BASIS-T on student outcomes via the mechanisms of implementation behavior change and if those effects are moderated by teacher factors and school contextual factors. We will also explore how mechanisms are linked to implementation outcomes for “hypothesis-defying residuals” (i.e., teachers whose attitudes, subjective norms, and self-efficacy surrounding EBPP implementation are inconsistent with their documented implementation behaviors).*RQ 2a*. Are the effects of BASIS-T mediated via mechanisms of behavior change?*RQ 2b*. Are the effects of BASIS-T on implementation and student outcomes moderated by teacher-level factors (e.g., demographics, stress, baseline intentions to implement) and school-level factors (e.g., geographic location, school demographics, supportive leadership, implementation climate)?*RQ 2c*. What explains “residual” teachers whose implementation behaviors are not accounted for by the mediation model?*RQ 2d.* What are the costs and cost-effectiveness of BASIS-T?

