We will use thegeneralizer.org to compare our sample to national demographics to examine the generalizability of our findings [58]. If not generalizable, we will use inverse probability weighting to increase the representativeness of estimates [87].*RQ 1a*: A series of 3-level piecewise mixed effects models will be used to test our primary hypotheses: (1) the BASIS-T condition will show steeper gains than the ACC condition from T1 to T2 (e.g., more favorable attitudes towards EBPPs, increased social norms; enhanced task and maintenance self-efficacy; stronger intentions to implement) and (2) both groups will decline after training (T3–T5) as has been found in past TPB research [88], and in the BASIS-T pilot trial [33], but the BASIS-T condition will have longer sustained between-condition effects after training from T3 to T13. Dependent variables will include subscale scores on attitudes, social norms, self-efficacy, intentions, and maintenance self-efficacy.*RQ 1b*: BASIS-T impact on behavioral implementation outcomes will be tested in two ways. First, a mixed effects model will examine whether the proportion of teachers in the BASIS-T condition who adopt PGD (i.e., initiate PGD) is higher than the proportion in the ACC condition. Second, Kaplan–Meier time-to-event analyses will be used to compare conditions on the number of days between training and PGD initiation. Reach will be analyzed using mixed effects models comparing BASIS-T vs. ACC on the proportion of students in each classroom (out of those eligible based on whether their classroom teacher participated in PGD training) who received PGD practices. Impact on PGD fidelity will be analyzed using mixed effects models with sessions within teachers, testing for the main effects of condition on adherence and participant responsiveness ratings derived from both PGD observational and self-report fidelity data. We will test the effects of BASIS-T on PGD sustainment and delayed implementation using the multilevel longitudinal analytic approach described for RQ1a.*RQ1c*: BASIS-T impact on student SEB and academic outcomes will be tested via mixed effects multilevel models as described in RQ1a, with academic data aggregated to the classroom level. Dependent variables will include post-intervention scores on teacher ratings of student behavior.*RQ2a*: Whether mechanisms of behavior change mediate the impact of BASIS-T on implementation outcomes will be analyzed using path analysis [89] extending traditional mediation modeling to a multi-level framework for nested data [90, 91].*RQ2b*: To test whether the effect of BASIS-T on implementation and student outcomes is moderated by teacher factors (e.g., demographics, baseline intentions to implement) and school-level factors, we will add moderators and interaction terms to the analytic approach described in RQs 1a-c.*RQ2c*: To explore what explains “residual” teachers whose implementation behaviors are not accounted for by the mediation model, we will analyze qualitative interviews with teachers who have a difference between predicted (based on BASIS-T putative mechanisms) and actual implementation behavior of ≥ 1 SD. Data will be coded using an integrated directed and conventional content analysis [92] approach as certain codes will be conceptualized during the interview guide development and driven by the exploration, preparation, implementation, sustainment [93] framework (i.e., deductive approach) which will allow for the examination of influences on implementation across multiple levels and phases. Other codes will be developed through a close reading of an initial subset of transcripts (i.e., inductive approach). These themes will provide a way of identifying and understanding the most salient factors that impact implementation and extend beyond the existing BASIS-T mechanisms and theory of change. After a stable set of codes is developed, a consensus process will be used in which all reviewers independently code and compare their coding to arrive at consensus judgments through open dialogue [78, 79, 94].*RQ2d*: We will process cost data by assigning monetary values to each cost. We will use CostOut [95], a web-based program for conducting cost-effectiveness analysis in education, to identify nationally representative unit prices for ingredients. For qualitative data, we will rapidly analyze responses on an ongoing basis [96, 97] and incorporate newly identified costs into future surveys for quantitative measurement.

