#### Power

Our planned sample, including attrition, will provide sufficient power to test linear effects on teacher- and classroom school-level variables with a minimum detectable effect size (MDES) of small to medium effects, *d* = 0.37. We used PowerUp! [100] assuming clustering, final samples of 46 schools evenly randomized to condition, 6 teachers per school (after 15% attrition), school ICCs of 0.10 (consistent with our pilot data), and 13 timepoints. With the same assumptions as above, plus an assumption that 50% of the schools will be in a given moderator subgroup, our MDES for detecting any single school-level moderator variable is 0.48 and teacher-level moderator variable is 0.45. For mediator analyses, PowerUp! identifies power using the Sobel test, joint test, and Monte Carlo simulations. Across all tests, we will have a power of greater than 0.80 to detect reasonable and likely effects, based on our pilot trial and standard interpretations of effect sizes. We will detect an MDES equivalent to Cohen’s *d* = 0.60 for the treatment-mediator pathways (e.g., BASIS-T to implementation intention) which is lower than our actual obtained effect size from the pilot trial (which ranged from *d* = 0.61 to 1.16 for our primary mediators), an MDES of Pearson’s *r* = 0.3 for the mediator-outcome path (e.g., implementation intention to student behavior, a small effect), and an MDES of *d* = 0.10 for the direct path from treatment to student outcome.

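### Aim 2 announces mediation of BASIS-T effects on student outcomes, but the only planned mediation analysis (RQ2a) names implementation outcomes alone

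*Protocol article*

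**What the plan says.** The abstract (Methods) describes Aim 2 as "testing whether the effects of BASIS-T on child outcomes are (a) mediated via its putative mechanisms of behavior change". Objectives and aims repeats this: "Aim 2 will evaluate the effects of BASIS-T on student outcomes via the mechanisms of implementation behavior change". The research question listed under that aim names no outcome: "Are the effects of BASIS-T mediated via mechanisms of behavior change".

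The Data analytic plan then gives one mediation analysis, under RQ2a: "Whether mechanisms of behavior change mediate the impact of BASIS-T on implementation outcomes will be analyzed using path analysis". Student outcomes are not mentioned there.

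The Power section returns to students. It gives a minimum detectable r of 0.3 for the "mediator-outcome path (e.g., implementation intention to student behavior, a small effect" and a minimum detectable d of "0.10 for the direct path from treatment to student outcome".

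**The concern.** The aim and the power basis point to one endpoint, and the analysis points to another. This is not a detail that a condensed article leaves out. The article does state an endpoint for RQ2a, and it differs from the one its own aim announces.

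What is at stake is the Aim 2(a) result. If the plan is followed to the letter, the trial will report whether the mechanisms explain differences in implementation, and will have no model that says whether they explain differences in students. If a student-outcome model is fitted later, a reader of this article could see that the aim was published in advance, but not that the analysis was. The mediation power statement would also describe tests that are not in the plan.

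**Working it through.** No arithmetic decides this point. The check is to set the places that name an endpoint side by side, and then to see whether any other planned analysis fills the gap.

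**Endpoint of the mediation, by place**

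| Place in the protocol article | Endpoint named |
|---|---|
| Abstract, Methods | Child outcomes |
| Objectives and aims, Aim 2 | Student outcomes |
| Objectives and aims, RQ2a question | None |
| Data analytic plan, RQ2a | Implementation outcomes |
| Power, mediator-outcome path (r = 0.3) | Student behavior, given as the example |
| Power, direct path (d = 0.10) | Student outcome |

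Four entries name children or students, one names no outcome, and the one that specifies the analysis names implementation.

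**Does another analysis supply the missing test?**

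1. RQ1c covers student outcomes: "BASIS-T impact on student SEB and academic outcomes will be tested via mixed effects multilevel models as described in RQ1a". This is the effect of condition. No mediator enters the model.
2. RQ2b covers both outcome sets: "To test whether the effect of BASIS-T on implementation and student outcomes is moderated by teacher factors". This is moderation. It may bring baseline intentions into a student-outcome model, but as an effect modifier and not as a mediator. It also shows that the article lists both outcome sets when it means both. The RQ2a text just before it lists only one.
3. RQ2c selects teachers whose implementation differs from what the mechanisms predict. That needs an implementation endpoint and says nothing about students.
4. RQ2d computes cost-effectiveness ratios for implementation and student measures. It contains no mediation.

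None of the four is a mediation model with a student endpoint.

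**Which power figures match the RQ2a analysis?**

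- Treatment to mechanism, d = 0.60: usable for either endpoint.
- Mechanism to outcome, r = 0.3: illustrated with student behavior.
- Direct path, d = 0.10: student outcome, stated without qualification.

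So one of the three mediation figures fits RQ2a as written. The d = 0.10 cannot simply be reassigned to RQ1c. It appears among the mediation paths, and the Power section gives a separate main-effect figure of d = 0.37.

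**The case against.** The strongest reply is that the intention is clear. The abstract, the aim and the Power section all announce mediation to student outcomes, the RQ2a question leaves the outcome open, and the conflict comes down to one phrase in a condensed article. The full analysis plan may give the complete path model. On this view, adding student outcomes would carry out a published aim and would not be a post hoc choice. Much of this stands. Student mediation was probably intended, and RQ2a was probably worded too narrowly. That makes the correction easy but does not resolve the conflict, because the text still states an endpoint that contradicts the aim. It is also fair that the r = 0.3 is introduced by an example and may have been meant more generally. Even so, no mediator-outcome figure is stated for implementation, and the direct-path figure is given for students without qualification.

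Stronger readings are tempting and are not supported:

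- A reader might infer that Aim 2 as a whole goes untested. It does not: RQ2b and RQ2d both reach student outcomes.
- A reader might infer that the endpoint mismatch undermines the residual-teacher interviews. RQ2c is defined by implementation behavior, so the implementation-endpoint model is the one it needs.
- A reader might multiply the power figures along a chain from mechanism to implementation to student, to argue that the effect on students must be much smaller than the effect on implementation. The article gives no correlation for mechanism to implementation or for implementation to student. Its r = 0.3 is illustrated on the direct link from mechanism to student behavior. The figures are also minimum detectable effects, not expected ones.

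**Conclusion.** The point holds for the mediation part of Aim 2. No planned mediation model tests the effect that Aim 2(a) announces. Two of the three mediation power figures (r = 0.3, as illustrated, and d = 0.10) are attached to a student endpoint that RQ2a does not name, and the endpoint it does name has no stated mediator-outcome figure. The size is one announced test without a matching analysis. No numerical bias or loss of power follows, and the values of the power figures are not disputed here.

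The conclusion rests on the article's wording alone. A statistical analysis plan may exist and may already specify the longer model; in that case only the article's text needs reconciling. The main-effect analyses and RQ2b to RQ2d stand as they are. The matter should be corrected before the mediation analysis is run, but it does not threaten the trial's primary hypotheses.

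**What to change.** Extend the RQ2a multilevel path analysis so that it covers student outcomes as well as implementation outcomes. The student path can run directly from mechanism to student outcome, which is the link the Power section uses as its example, or through implementation. Either would meet the aim, and the choice belongs to the investigators. Then:

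- name the indirect effect on student outcomes as the Aim 2(a) test;
- keep the path ending at implementation, because RQ2c depends on it;
- state in the Power section which figure belongs to which path, and add a mediator-outcome figure for implementation.

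If mediation was meant to stop at implementation, leave RQ2a alone and restate the abstract, Aim 2 and the mediation power paths to match.

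The student data need no new collection: the Quantitative surveys section already provides for teacher ratings of classroom behavior and end-of-year records at classroom level. The cost is one further model and some added power work, more if the path runs through implementation, since the article powers no three-link chain. Student outcomes would also add dependent variables to the false-discovery-rate adjustment that the plan applies within a research question. The alternative fix costs only wording, but gives up the student-level mediation claim.

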#### Preliminary BASIS-T studies

The BASIS strategy was developed via an iterative user-centered design approach [46]. Initial pilots of BASIS-T and a version designed for school-based mental health clinicians (BASIS-C) have demonstrated promise in enhancing participants’ attitudes, subjective norms, self-efficacy, and adoption [30, 33, 47]. The BASIS-T pilot study on which the current project is based was an attention-control randomized trial conducted with 82 elementary school teachers implementing a universal, classroom-based EBPP [48–50]. That study found a statistically significant positive impact on implementation task self-efficacy and outcome expectancy immediately after training and significantly less decline in task self-efficacy than attention control throughout the academic year [33]. Positive attitudes towards evidence-based practices decreased for both groups over time but with a marginal time trend in favor of less decrease for the BASIS-T condition (*p* = 0.08). Except for ownership/role, all other mechanisms (outcome expectancies, subjective norms, self-efficacy, and intentions to implement) deteriorated for both groups after the post-BASIS timepoint (i.e., during active implementation), yet all effect sizes were in favor of less deterioration in the BASIS-T condition. Significantly higher proportions of teachers in BASIS-T immediately adopted the EBPP (74% of BASIS-T condition, 40% of attention control). With marginal significance, fidelity to the EBPP remained steady for the BASIS-T group over time but deteriorated for attention control (*p* = 0.052), and the BASIS-T condition engaged in the EBPP more frequently (*p* = 0.097). A preliminary analysis estimated the cost of BASIS-T at $256 per teacher based on time and material costs. Notwithstanding the promise of these findings, this was an underpowered pilot trial designed to lay a foundation for the current study.

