#### Cost assessments

Cost data collection will occur with all participating teachers to capture major costs of PGD delivery with and without BASIS-T, using activity-based costing to focus on key expenses (e.g., teacher and staff time, materials) [80, 81]. We will measure costs from the payor (i.e., school system) perspective, since the primary costs and associated decision-making would be within the implementing school system in real-world implementation. These data will be collected along with other study measures depending on how often an item needs to be measured (e.g., one-time training prep in time 4 vs. PGD delivery collected monthly alongside the fidelity measures). Following expert guidance to use mixed methods in implementation cost studies [82], we will include open-ended items in each survey asking teachers to identify unexpected resources they have needed for BASIS-T or PGD. ACC costs will be excluded from the cost estimate for the comparison condition; PGD implementation-as-usual is the ideal counterfactual for the cost-effectiveness of BASIS-T because it represents “business as usual” for PGD and, unlike BASIS-T, ACC would never be delivered outside of a research project. To develop complete cost estimates for BASIS-T versus PGD implementation-as-usual, we will combine the teacher-reported data with information from other sources, such as BASIS-T training records and meetings with school partners.

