
Once cost data collection is complete, we will calculate the costs of BASIS-T versus PGD implementation-as-usual based on the unit price and amount of each cost category (e.g., hours spent, items purchased). We will use CostOut to standardize dollar values, including an index year for inflation; cost-of-living adjustments; and discounting costs from different years to account for preferencing of delayed over immediate costs [80, 95]. We will generate descriptive statistics describing typical costs (i.e., means, standard deviations) for each condition and incremental costs of BASIS-T over implementation as usual.

Once the cost analysis is complete, we will use CostOut to calculate the cost-effectiveness [81] of BASIS-T versus PGD implementation as usual. This will involve calculating a series of incremental cost-effectiveness ratios for each implementation and student outcome measure, representing the incremental costs of BASIS-T divided by its incremental benefit (i.e., effect size). Themes about BASIS-T mechanisms and outcomes from the qualitative teacher interviews will allow for mixed-method cost-effectiveness evaluation [82] in which participants’ views help determine whether the results were worth the cost. For both cost and cost-effectiveness analyses, we will conduct sensitivity analyses that vary key sources of uncertainty in the models to examine the robustness of our estimates [98, 99].

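### RQ2d fixes a cost-per-effect-size ratio for every outcome, a summary that breaks down when the estimated effect is near zero or adverse

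*Protocol article*

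**What the plan says.** The RQ2d text at the end of the Data analytic plan section has two steps.

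- **Costs.** Means and standard deviations are given by condition, together with the "incremental costs of BASIS-T over implementation as usual".
- **Cost-effectiveness.** The analysis consists of "calculating a series of incremental cost-effectiveness ratios for each implementation and student outcome measure", each "representing the incremental costs of BASIS-T divided by its incremental benefit (i.e., effect size").

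The same text adds a qualitative judgement of whether results were worth their cost, and a general commitment: "we will conduct sensitivity analyses that vary key sources of uncertainty in the models to examine the robustness of our estimates". It does not say what is reported when the effect is null or adverse.

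Three other places bear on the numerator and denominator.

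- **Cost assessments:** "ACC costs will be excluded from the cost estimate for the comparison condition", so BASIS-T enters as an add-on to PGD as usual.
- **Preliminary BASIS-T studies:** "A preliminary analysis estimated the cost of BASIS-T at $256 per teacher based on time and material costs".
- **Power:** a main-effect "minimum detectable effect size (MDES) of small to medium effects, *d* = 0.37" and, in the mediation calculation only, "an MDES of *d* = 0.10 for the direct path from treatment to student outcome".

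**The concern.** A ratio with a positive numerator behaves well only while its denominator stays clear of zero on the beneficial side. This plan applies it to every outcome, including student outcomes two steps removed from the strategy: BASIS-T acts on teachers, teachers deliver PGD, and PGD acts on classrooms. Effects there may be small relative to their standard error. In that region the ratio is unstable, can change sign, and loses its ordering once negative.

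The direction of the effect adds an ambiguity. Disruptive behaviour and discipline improve by going down. The article equates benefit with effect size without stating a common direction, so the sign of a ratio alone does not show which way an outcome moved.

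Costs and cost-effectiveness form a stated research question, and the Conclusion promises evidence on cost-effectiveness. A series of ratios that mixes stable, exploding and negative values would serve that purpose poorly.

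**Working it through.** **Inputs.** Incremental cost $256 per teacher (pilot), held fixed; the trial's own increment will differ. From the Power section: 46 schools split evenly, 6 teachers per school, school ICC 0.10, MDES 0.37. Assumed, because not stated for this MDES: two-sided 5% test, 80% power, 44 degrees of freedom, which gives a multiplier M of about 2.865.

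**Step 1: standard error of d.**

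- Without covariates: SE = sqrt[0.10/(0.25 × 46) + 0.90/(0.25 × 46 × 6)] = sqrt(0.00870 + 0.01304) = 0.147. The MDES is then 2.865 × 0.147 = 0.42.
- The stated 0.37 is reached with a choice the article does not spell out. A one-sided test gives 0.373. Covariates explaining about a quarter of the variance at both levels give 0.366. A three-level model with half the variance at teacher level gives 0.367.
- Taking 0.37 as stated and two-sided: SE = 0.37/2.865 = 0.129.

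The working range is therefore 0.129 to 0.147.

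**Step 2: the ratio itself.**

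- d = +0.10: 256/0.10 = $2,560 per SD
- d = -0.05: 256/(-0.05) = -$5,120 per SD
- d = -0.10: 256/(-0.10) = -$2,560 per SD

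Doubling the harm halves the size of the negative ratio. An estimate within 0.02 of zero gives a ratio larger than 256/0.02 = $12,800 in absolute size.

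**Step 3: how often the ratio is negative.** With positive cost, P(negative) = Φ(-d/SE).

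| True d | SE 0.129 | SE 0.147 |
|---|---|---|
| 0 | 50% | 50% |
| 0.10 | 22% | 25% |
| 0.20 | 6% | 9% |
| 0.37 | 0.2% | 0.6% |

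At a true d of 0.10, the estimate also falls within 0.02 of zero about 9% of the time at either SE.

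**Step 4: spread.** Simulating estimates with SE 0.129 and cost $256, the central 95% of ratios runs from about -$23,000 to +$24,200 when the true d is 0.10 (nominal value $2,560). When the true d is 0.37 it runs from about $410 to $2,100 (nominal value 256/0.37 = $692).

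**Step 5: several outcomes.** Aim 1 lists six student outcomes and the Abstract adds discipline, so about seven. At a true d of 0.10 for each, the chance of at least one negative ratio under independence is 1 - (1 - 0.219)^7 = 82%, or 1 - (1 - 0.249)^7 = 87% at the larger SE. Under perfect correlation it stays at the single-outcome 22-25%.

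**The case against.** **A negative ratio would not mislead.** A reader might infer that a harmful result would pass for a cost saving. The documents do not support that. Incremental cost is reported separately and is expected to be positive, so a negative ratio beside it can be recognised as higher cost with a worse effect. Nor does the article propose to rank outcomes by their ratios. This part of the objection stands.

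**The d of 0.10 is not an expected effect.** Correct: it is a detectable effect for one mediation path, and the article states no expected student effect. At face value that MDES would imply an SE of 0.10/2.865 = 0.035 and negative ratios only 0.2% of the time at d = 0.10. That precision is hard to square with the same sample, though. Even with no clustering, 276 teachers give an SE of sqrt(1/69) = 0.12, and reaching 0.035 would need about 92% of the variance explained. I therefore use the main-effect SE and treat 0.10 as one illustrative value among several.

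**Unbounded confidence intervals.** One might infer that most intervals for student ratios will have no finite limits. That is a property of Fieller intervals for non-significant effects, and the article commits to no interval method, so I do not rely on it.

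**Detail belongs to the full analysis plan.** Interval methods, outcome orientation and the handling of dominated results may well be set there, and their absence from an article is not a fault. The choice of summary and its scope are different, because the article itself fixes both. The promised sensitivity analyses may help, but nothing says that they replace the ratio.

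**Implementation outcomes may be unaffected.** Fair. Pilot adoption was 74% against 40%, and an effect that clear would give a stable ratio. The difficulty lies mainly with student outcomes and with any implementation outcome showing little difference.

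**Conclusion.** The point holds as a poorly chosen summary that the plan states outright. A cost-per-effect-size ratio for every outcome is interpretable only where benefit is clear, and the plan makes no exception. With an SE of 0.13 to 0.15, a negative ratio is fairly common at a true d of 0.10 (22-25% per outcome), occasional at 0.20 (6-9%) and rare at 0.37 (under 1%). For about seven student outcomes at d = 0.10, the chance of at least one lies between about 22% and 87%. The upper end needs independence, which is unlikely because three of the outcomes are ratings by the same teacher of the same classroom.

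These figures assume a fixed positive cost of $256, normally distributed estimates and the Power section's design values. They illustrate how the rule behaves and do not predict the trial's results. The effect comparisons under Aim 1 are untouched.

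**What to change.** In the RQ2d text:

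- Report for each outcome the pair of incremental cost and incremental effect, with every outcome oriented so that positive means benefit (disruptive behaviour and discipline reversed).
- Obtain joint uncertainty from a bootstrap that resamples whole schools, and show it on the cost-effectiveness plane.
- Where the effect estimate is zero or adverse, write *more costly, no benefit* or *dominated* in place of a ratio.
- Where a ratio is given, show it with its joint uncertainty, and do not rank ratios across outcomes.

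I would not limit ratios to statistically significant outcomes, since that selects inflated effects. Nor would I require willingness-to-pay curves, since the article gives no monetary value for one SD of classroom behaviour.

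The cost is a change of wording and a bootstrap on data already to be collected. There will be fewer single-number ratios to quote, and the bootstrap may have to be run outside CostOut.
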